## Abstract

**Background:**

The purpose of this study is to evaluate the predictive accuracy of a machine learning-based herbal medicine response prediction algorithm in patients with functional dyspepsia (FD). In a preliminary clinical study, the algorithm was developed using the XGBoost regressor framework to predict the relative effect sizes of three commonly prescribed herbal formulations—*Yijung-tang* (*Lizhong-tang*), *Pyeongwi-san* (*Pingwei-san*), and *Shihosogan-tang* (*Chaihu Shugan-tang*). The prediction system recommends the formulation expected to yield the greatest therapeutic benefit for each individual.

**Methods:**

This study is a randomized, assessor-blinded, parallel-group, open-label, multicenter clinical trial. A total of 100 patients with FD will be recruited from two Korean medical hospitals and randomly assigned to either the ACCORD group (*n* = 50), which will receive treatment guided by the machine learning algorithm, or the DISCORD group (*n* = 50), which will receive one of the two treatments not recommended by the algorithm. Patients will take the assigned herbal medicine for 8 weeks, three times daily, between meals.

**Outcomes:**

The primary outcome will be gastrointestinal symptom score. Secondary outcomes will include total dyspepsia symptom score, adequate relief of dyspepsia, overall treatment effect, visual analog scale score, functional dyspepsia–related quality of life, and pattern identification questionnaire results. Exploratory outcomes will include blood and fecal metabolome analysis, fecal and salivary microbiota profiling, and measurements obtained using Korean medicine diagnostic devices (heart rate variability, tongue, pulse, and abdominal diagnosis).

**Conclusion:**

Integrating a machine learning-based prediction system into treatment strategies for FD may enhance clinical practice and support the broader adoption of artificial intelligence-driven approaches in personalized medicine.

**Clinical trial registration:**

Clinical Research information Service (registration number: KCT0010587) and Open Science Framework (https://osf.io/2ecz8).

## Introduction

1

Functional dyspepsia (FD) is a medical condition characterized by one or more of the following symptoms: postprandial fullness, early satiation, epigastric pain, and epigastric burning, which remain unexplained after routine clinical evaluation. FD is classified into two subcategories: postprandial distress syndrome (PDS), characterized by meal-induced dyspeptic symptoms, and epigastric pain syndrome (EPS), which does not occur exclusively postprandially; the two subgroups may also overlap. The pathophysiology of FD is complex, multifactorial, and not fully elucidated (1). The global prevalence of FD is estimated at 21%, although rates vary substantially between countries (2).

Conventional treatments for FD focus on symptom management, primarily through medication, with treatment durations typically limited to 8–12 weeks due to the absence of curative options (3). Acid suppressants, such as proton pump inhibitors, are mainly used for patients with EPS, whereas prokinetics are primarily prescribed for PDS with gastrointestinal motility issues. If these medications are ineffective, fundus-relaxing drugs may be used for PDS, and further treatment options include antidepressants or psychotherapy (4). However, these treatments are not universally effective, and most act by blocking specific neurotransmitter receptors, which can cause side effects such as extrapyramidal symptoms (5), QT interval prolongation (6), dizziness (7), and loss of appetite (8).

To address these limitations, traditional Korean medicine offers alternative treatments, such as herbal medicine and acupuncture, which are actively practiced worldwide (9). In Korea, clinical practice guidelines for FD in traditional Korean medicine have been developed, recommending herbal treatments for symptom improvement and maintenance. Notable prescriptions include *Banhasasim-tang*, *Yukgunja-tang*, *Soyo-san*, *Pyeongwi-san*, and *Shihosogan-san* (10). Traditional Korean medicine categorizes FD into six syndromic patterns: spleen and stomach deficiency–cold, spleen and stomach damp–heat, tangled cold and heat, spleen deficiency with qi stagnation, liver–stomach disharmony, and food retention disorder (11). In a study by Ha et al. (11), 95 patients with FD were analyzed, revealing that spleen and stomach deficiency–cold was the most prevalent pattern, accounting for 52% of cases, followed by spleen and stomach damp–heat (14.7%), tangled cold and heat (13.7%), spleen deficiency with qi stagnation (9.5%), liver–stomach disharmony (7.4%), and food retention disorder (3.2%).

Diagnosis in traditional Korean medicine is conducted through four phases: inspection, listening and smelling, inquiry, and palpation. Practitioners integrate correlations between the symptoms and signs presented by the patient to perform pattern identification, which guides the selection of appropriate treatments (12). Although recent advancements have led to the development of standardized questionnaires for quantitative assessments of specific patterns—such as spleen and stomach deficiency–cold, spleen and stomach damp–heat, and food stagnation in patients with FD—the diagnostic protocols in clinical practice remain heavily reliant on traditional methods, resulting in a process that is subjective and lacks standardization (13). To address these challenges, the integration of modern science with traditional Korean medicine, particularly through artificial intelligence (AI), has been proposed as a promising approach. AI has the potential to analyze data-driven insights and predict herbal medicine responses, thereby enabling more personalized and effective treatment strategies (14).

Empirically, herbal formulations such as *Yijung-tang* (*Lizhong-tang*, YJT) for spleen deficiency (15, 16), *Pyeongwi-san* (*Pingwei-san*, PWS) for food stagnation (17), and *Shihosogan-tang* (*Chaihu Shugan-tang*, SST) for liver depression (18) are widely used in the treatment of FD. In a preliminary study, these formulations were administered to patients with FD to develop an machine learning-based predictive algorithm for anticipating herbal medicine responses (19). Over an 8-week treatment period, data were collected from various sources, including blood, fecal, and saliva samples, as well as questionnaires and traditional diagnostic devices. This comprehensive dataset was used to construct the machine learning-based prediction system, which was designed to propose typical pattern differentiation types. Building on this foundational work, the present study aims to validate the predictive accuracy of the machine learning-based prediction algorithm. By randomly assigning patients with FD to receive YJT, PWS, or SST based on the machine learning prediction—or one of the remaining herbal medicines not determined by the algorithm—the study seeks to enhance the objectivity and reproducibility of traditional Korean medicine treatments. This approach may provide a pathway toward more personalized and effective patient outcomes.

## Methods

2

### Study design and setting

2.1

#### Study design and allocation

2.1.1

This study is a randomized, assessor-blinded, parallel-group, open-label, multicenter clinical trial. It will be conducted at two Korean medical hospitals: Kyung Hee University Hospital at Gangdong and Dongguk University Ilsan Oriental Medical Hospital. Participants who voluntarily sign the informed consent form will undergo screening examinations during their initial visit (screening visit), including interviews, vital sign measurements, questionnaire surveys, assessments with Korean medicine diagnostic devices, and laboratory tests. Eligible participants will then be enrolled. Within 2 weeks of the screening visit, participants will be randomly assigned to either the ACCORD group, which will receive YJT, PWS, or SST based on a machine learning–driven herbal response prediction algorithm, or the DISCORD group, which will be randomly assigned one of the two herbal medicines not selected by the prediction algorithm from the three options. This ACCORD vs. DISCORD design is specifically employed to validate the algorithm’s discriminative ability—that is, whether the algorithm can accurately distinguish the optimal treatment from suboptimal alternatives for an individual patient. This validation of predictive accuracy is a necessary step before evaluating clinical utility against standard care.

The machine learning algorithm employed in this trial was developed in a prior preliminary clinical study (*N* = 265) (19) (the resulting paper detailing the development methodology is currently under review; Supplementary material 1). The algorithm utilizes the XGBoost (Extreme Gradient Boosting) regressor framework. The objective of the model is a regression task: to predict the magnitude of symptom improvement (effect size) for each of the three herbal formulations (YJT, PWS, and SST). The prediction system recommends the formulation expected to yield the greatest therapeutic benefit for the individual.

The ground truth (target variable) for model training was the observed change in the Gastrointestinal Symptom (GIS) score from baseline to 8 weeks in the preliminary study. The models were trained using comprehensive baseline data as input features. These features included demographics (e.g., age, sex, and FD duration); patient-reported outcomes and questionnaires (e.g., GIS, and various pattern identification questionnaires); data from Korean medicine diagnostic devices (e.g., tongue diagnosis system, radial pulse analyzer, and digital algometer readings); and laboratory test results (e.g., blood chemistry).

During development, the dataset was split into training (80%) and test (20%) sets for internal validation. Hyperparameter tuning was conducted using RandomizedSearchCV with 5-fold cross-validation on the training data. To mitigate overfitting due to high data dimensionality, an iterative feature selection process was employed to enhance model robustness. The final models demonstrated robust predictive accuracy on the independent test set, confirming their capability to predict treatment responses and discriminate the relative effectiveness among the herbal formulations. Detailed methodology of the algorithm development is provided in Supplementary material 1. The algorithm for prediction system employed in this trial is a locked version (v1.1) that will not be updated during the study period. The prospective validation of this locked algorithm in a new cohort is essential for evaluating its generalizability and mitigating potential biases or overfitting inherent in the preliminary training dataset.

All groups will take the assigned clinical trial medications for 8 weeks. Participants will attend clinic visits at 4-week intervals until week 8 for evaluation of clinical variables, including vital signs, questionnaire surveys, and assessments with Korean medicine diagnostic devices (heart rate variability [HRV], tongue diagnosis, pulse diagnosis, and abdominal diagnosis). In addition, telephone visits will be conducted at 2-week intervals (weeks 2 and 6) to assess whether FD-related pain or discomfort has moderately improved since the previous treatment (Figure 1). Before and after taking the herbal medicine, blood samples (at screening and week 8) and stool and saliva samples (at weeks 0 and 8) will be collected to analyze blood and fecal metabolites as well as gut and oral microbiomes. A detailed assessment schedule is provided in Table 1.

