#### Randomization and blinding

2.1.2

Participants will be divided into the ACCORD group, assigned herbal medication by the machine learning-based prediction algorithm, and the DISCORD group, which will not use the prediction algorithm. For example, if the prediction algorithm assigns YJT, the group receiving YJT will constitute the ACCORD group, whereas those receiving PWS or SST will constitute the DISCORD groups. Randomization will be stratified by each herbal medicine using block randomization to minimize bias before the clinical trial begins. For each stratification factor, the group allocation ratio will be 1:1 (ACCORD: DISCORD), with block sizes of 4 and 8. The DISCORD group will then be divided into two subgroups, excluding the optimal herbal medicine per the prediction algorithm, and randomly assigned, resulting in a 2:1:1 allocation (ACCORD: DISCORD_1: DISCORD_2). To prevent bias toward a specific herbal medicine, the maximum number of participants assigned to any single herbal medicine will be capped at 48. Any additional participants for that medicine will be excluded during screening.

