### Sample size calculation

2.7

Participants will be randomly assigned to either the ACCORD group, which will receive YJT, PWS, or SST based on the machine learning–driven prediction, or the DISCORD group, which will not use the machine learning-based prediction for herbal assignments. Based on preliminary clinical trial results (19), the mean change in the GIS score after 8 weeks in both the ACCORD and DISCORD groups is assumed to be 2.72, with a standard deviation of 4.57. To meet this requirement, each group will require 45 participants. Considering a 10% dropout rate, the total required sample size is 100 participants. This sample size was determined for the prespecified primary comparison (ACCORD vs. pooled DISCORD) and was not inflated to power subgroup or stratified analyses, which will be considered exploratory.

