### Statistical analysis

2.8

All statistical analyses will be conducted using two-sided tests with a significance level of 5%. For continuous data, means and 95% confidence intervals will be presented, whereas categorical data will be presented as frequencies and percentages. All analyses will be performed using SAS® Version 9.4 (SAS Institute Inc., Cary, NC, United States).

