#### Statistical analysis and evaluation of efficacy endpoints

2.8.2

The primary efficacy endpoint is the between-group difference in the GIS score at week 8 (ACCORD vs. DISCORD). The primary endpoint will be analyzed using the MMRM, with treatment group and visit time as fixed factors and participant as a random factor.

The secondary efficacy endpoints include TDS, AR for dyspepsia, OTE, dyspepsia VAS, FD-QoL, Spleen Qi Deficiency Questionnaire, Stomach Qi Deficiency Questionnaire, Food Retention Questionnaire, Cold–Heat Pattern Questionnaire, and Deficiency–Excess Pattern Questionnaire. Categorical secondary variables will be analyzed using the chi-square test or Fisher’s exact test.

To address the issue of multiple comparisons for the multiple secondary efficacy endpoints, the Benjamini-Hochberg procedure (False Discovery Rate, FDR) will be applied to adjust the *p*-values. The primary endpoint will be tested at a significance level of 0.05 without adjustment. Exploratory outcomes will not be adjusted for multiplicity, and their results will be interpreted as hypothesis-generating.

Exploratory subgroup analyses (by assigned herbal formula and by DISCORD subgroup) will be performed to assess the consistency of treatment effects; these analyses are hypothesis-generating and are not powered for confirmatory inference. Effect modification will be explored using treatment-by-subgroup interaction terms within the mixed model, and results will be reported as effect estimates with 95% confidence intervals and interpreted cautiously.

For the primary outcome, missing data will be handled using the last observation carried forward (LOCF) method. In addition, multiple imputation will be applied as a sensitivity analysis to assess the robustness of results under different assumptions regarding missingness. The main analyses will be conducted on an intention-to-treat basis, with per-protocol analyses performed for comparison.

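### The ACCORD versus pooled DISCORD contrast estimates the mean benefit of following the algorithm; on its own it does not show discrimination at the level of the individual patient

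*Protocol article*

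**What the plan says.** Section 2.1.1 gives the purpose of the ACCORD versus DISCORD design as learning "whether the algorithm can accurately distinguish the optimal treatment from suboptimal alternatives for an individual patient".

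Section 2.7 fixes the contrast: "This sample size was determined for the prespecified primary comparison (ACCORD vs. pooled DISCORD"). Section 2.8.2 analyses the week-8 GIS score with a repeated-measures mixed model. It names group and visit as fixed factors and participant as random, with no term for the formula recommended or received.

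Section 2.1.2 stratifies randomisation by herbal medicine and allocates 1:1, then splits DISCORD equally between the two formulas not recommended (2:1:1). As protection against one formula dominating, "the maximum number of participants assigned to any single herbal medicine will be capped at 48", with any surplus excluded at screening.

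On formulas, section 2.8.2 adds: "Exploratory subgroup analyses (by assigned herbal formula and by DISCORD subgroup) will be performed to assess the consistency of treatment effects". These analyses are described as hypothesis-generating and unpowered, with effect modification explored through treatment-by-subgroup interaction terms.

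The Discussion's limitations cover the missing physician's-choice comparator and the low power of subgroups. They do not mention that average formula differences can enter the primary contrast.

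**The concern.** Stratifying by the recommended formula balances patient type between the arms. It does not balance which formulas the arms receive. Suppose one formula is better for everybody and the algorithm recommends it more than a third of the time. ACCORD then receives more of it than DISCORD and does better on average, even if the algorithm knows nothing about individual patients. The same happens if one formula is worse for everybody and is rarely recommended.

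The conclusion is what is at stake. A significant result could be reported as validating individual prediction when part of it reflects a difference between formulas that needs no algorithm.

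**Working it through.** **Inputs from the protocol article.** Two-sided 5% (section 2.8: "All statistical analyses will be conducted using two-sided tests with a significance level of 5" per cent). GIS change "is assumed to be 2.72, with a standard deviation of 4.57" (section 2.7). "To meet this requirement, each group will require 45 participants". "Considering a 10% dropout rate, the total required sample size is 100 participants". Allocation 2:1:1 and a cap of 48 (section 2.1.2).

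**Assumptions.** Power of 80% (none is stated), the recommendation shares, and the size of any average formula difference.

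**1. The plan's own figure.** Section 2.7 words 2.72 as the change in both groups. The stated n follows only if 2.72 is the between-group difference: n = 2 × (1.96 + 0.8416)² × 4.57² / 2.72² = 44.3, so 45 per group. Dividing by 0.90 gives 50 per group and 100 in total. At 45 per group, SE = 4.57 × √(2/45) = 0.963, power is 80.6%, and the smallest significant difference is 1.96 × 0.963 = 1.89.

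**2. Formula mix by arm.** If share p of patients is recommended a formula, ACCORD receives it at rate p and DISCORD at rate (1 − p)/2. The difference is 1.5p − 0.5, which is zero only at p = 1/3. With no patient-level matching at all, the expected primary difference is Σ(1.5pⱼ − 0.5)μⱼ, where μⱼ is the average effect of formula j.

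**3. Bounds if the cap limits recommendations (48 of 100).** The largest share is 0.48, with weight 1.5 × 0.48 − 0.5 = 0.22. The smallest possible share is 1 − 0.48 − 0.48 = 0.04, with weight 1.5 × 0.04 − 0.5 = −0.44. In that second case the third formula goes to 4% of ACCORD and 48% of DISCORD.

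**4. Size with 45 evaluable per arm and no individual prediction.**

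| Assumed mix | Assumed formula difference | Leak at 2.72 points | Chance of significance |
|---|---|---|---|
| Equal thirds | any | 0 | 5% |
| 48/26/26 | first formula better | 0.22 × 2.72 = 0.60 | 9.5% |
| 48/48/4 | third formula worse | 0.44 × 2.72 = 1.20 | 23.7% |

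For a formula difference of 1 point, the two unequal mixes give 0.22 points (5.6%) and 0.44 points (7.4%). For 4 points they give 0.88 (15.0%) and 1.76 (44.7%). For the leak alone to equal 1.89, the formula difference would have to be about 1.89/0.22 = 8.6 or 1.89/0.44 = 4.3 points.

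**5. If the cap counted recipients instead.** The number receiving a formula is 50p + 50(1 − p)/2 = 25 + 25p, which reaches 48 at p = 0.92. The weight is then 1.5 × 0.92 − 0.5 = 0.88. A 2.72-point advantage leaks 2.39 points, significant 70% of the time.

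**6. Can the two components be separated?** Yes. The three-by-three layout of recommended by received formula has nine cells. A model with an intercept, concordance, two recommended-formula terms and two received-formula terms has six parameters and full rank. Its cost for the concordance effect at 45 per arm:

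| Mix | Variance inflation | SE increase | Power for 2.72 |
|---|---|---|---|
| Equal thirds | 1.00 | 0% | 81% |
| 48/26/26 | 1.06 | 3% | 78% |
| 48/48/4 | 1.34 | 16% | 68% |
| 92/4/4 | 4.77 | 118% | 25% |

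**The case against.** **The cap is a real safeguard.** Surplus participants are excluded at screening, while Table 1 places allocation at the next visit, so only the recommendation can be known when the cap is applied. The value 48 is also a multiple of both block sizes. A reader might infer from the word assigned that 92% of patients could share one recommendation and that nearly 90% of a formula's advantage could leak through. The screening rule makes that the less plausible reading, so the 88% figure is a reason to clarify the text and not the expected case. Under the likelier reading the leak is bounded, and it is small for a single superior formula.

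**The subgroup analyses may be sound.** A reader might infer that the split by assigned formula compares non-randomised groups, because recipients of the same formula in the two arms had different recommendations. That holds only if assigned means received. Section 2.1.2 also uses the verb for the algorithm's choice; on that reading the subgroup is the randomisation stratum and the comparison within it is randomised. Likewise, a DISCORD subgroup exists in one arm only and cannot form a treatment interaction, but the article does not say that an interaction is fitted for every subgroup. Direct contrasts of ACCORD with each DISCORD subgroup within a stratum are valid.

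**An algorithm that picks a generally better formula has picked well.** This is fair, and it is why the primary contrast remains meaningful. It does not meet the claim as made, which concerns the individual patient.

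**Supportive models belong in the analysis plan.** One may well be there, in a document not shown. The point rests on what the article itself fixes: the claim, the contrast and the ambiguous cap.

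**Conclusion.** The point holds as one about inference. The primary comparison validly estimates the mean benefit of following the algorithm rather than receiving one of the two other formulas. A reader might go further and infer that the trial is biased or that its primary test is invalid. The documents do not support that, since the comparison is randomised within strata.

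What is unsupported is the step from a positive result to individual-level discrimination. The leak is zero with equal recommendation shares, which nothing in the article secures. With the cap on recommendations it is at most 22% of one superior formula's advantage or 44% of one inferior formula's deficit. The 0.60-point and 1.20-point figures rest on an assumed 2.72-point formula difference and assumed mixes; 48/48/4 is an extreme that the cap allows. The algebra is certain, but the size in this trial cannot be known from the article.

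**What to change.** Keep the primary test and the sample size. Then:

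- Prespecify a supportive mixed model for week 8 with concordance (ACCORD or DISCORD), recommended formula and received formula as fixed factors.
- Report the recommendation shares.
- Either base the conclusion about individual discrimination on the adjusted concordance effect, or narrow the conclusion to a mean benefit of following the algorithm.
- State that the cap and the assigned-formula subgroups refer to the recommended formula, that is, the randomisation stratum.
- Compare ACCORD with each DISCORD subgroup by direct contrasts and not through a treatment interaction.

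No new data are needed. The cost is precision: the concordance SE rises by 0% to 16% across the mixes that a cap on recommendations allows in the table above, and power for 2.72 can fall to about 68%. At 92/4/4 it would fall to about 25%. The adjusted analysis should therefore be labelled supportive, and a non-significant adjusted effect should not be read as evidence of no discrimination.

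### The pooled ACCORD vs DISCORD test shows that the recommendation beats the average of the other two formulas, not that it beats the predicted second choice

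*Protocol article*

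**What the plan says.** All references are to the protocol article.

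- **Purpose.** Section 2.1.1 (Study design and allocation) states that the ACCORD/DISCORD design is there to test "whether the algorithm can accurately distinguish the optimal treatment from suboptimal alternatives for an individual patient".
- **Algorithm output.** The same section says the model's task is "to predict the magnitude of symptom improvement (effect size) for each of the three herbal formulations", and that the formula with the largest predicted benefit is recommended. A predicted second and third choice therefore exist for every participant before randomisation.
- **Comparator.** DISCORD participants are "randomly assigned one of the two herbal medicines not selected by the prediction algorithm from the three options" (Section 2.1.1). Section 2.1.2 (Randomization and blinding) describes the split as "resulting in a 2:1:1 allocation (ACCORD: DISCORD_1: DISCORD_2". It identifies the two subgroups only as what remains once the recommended formula is removed; predicted rank is not mentioned.
- **Primary test.** Section 2.8.2: "The primary efficacy endpoint is the between-group difference in the GIS score at week 8 (ACCORD vs. DISCORD". Section 2.7 (Sample size calculation) names the "prespecified primary comparison (ACCORD vs. pooled DISCORD" as the basis of the sample size.
- **Subgroups.** Section 2.8.2: "Exploratory subgroup analyses (by assigned herbal formula and by DISCORD subgroup) will be performed to assess the consistency of treatment effects". These analyses are labelled hypothesis-generating and unpowered, and are to be reported with 95% confidence intervals.

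**The concern.** To call the recommended formula optimal among three, it has to do better than the runner-up. The primary contrast gives the second and third choices about equal weight, so a poor third choice can carry the whole difference. This is so even if the three formulas work equally well on average and are recommended equally often; it comes from pooling the two ranks.

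At stake is the sentence that can be written after a positive result. An algorithm that only rules out the worst of three formulas, or even one that ranks the best formula second, could produce a significant primary result. Read against the purpose in Section 2.1.1, that result would look like evidence that the algorithm finds the best formula.

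**Working it through.** **Inputs.** Difference 2.72, SD 4.57, 45 evaluable per group, 10% dropout, 100 in total (Section 2.7); two-sided 5% (Section 2.8); 2:1:1 allocation (Section 2.1.2). Assumed: 80% power, which is not stated, and 2.72 read as the between-group difference. Section 2.7 literally attaches 2.72 to both groups, but the sample size reproduces only under the between-group reading.

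**Step 1. Reproduce the plan's figure.** n per group = 2 × (1.96 + 0.8416)² × 4.57² / 2.72² = 44.3, rounded up to 45. Then 45 / 0.9 = 50 per group, 100 in total. It reproduces.

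**Step 2. What the primary contrast estimates.** Let a be the advantage of the pick over the second choice and b its advantage over the third, in GIS points of benefit. With DISCORD split equally, the contrast is (a + b) / 2. The planned 2.72 arises equally from:

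- a = 2.72, b = 2.72
- a = 1.36, b = 4.08
- a = 0, b = 5.44
- a = −1, b = 6.44

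**Step 3. How often the primary test favours ACCORD.** Simulated two-sample t-tests at week 8, SD 4.57 within each rank, 40,000 runs, counting significant results in ACCORD's favour. At 45 per arm DISCORD was split 23/22 and 22/23 (second/third); at 50 per arm, 25/25.

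| a (vs second) | b (vs third) | 45 per arm | 50 per arm |
|---|---|---|---|
| 2.72 | 2.72 | about 80% | 84% |
| 1.36 | 4.08 | 77–79% | 83% |
| 0 | 5.44 | 73–77% | 79% |
| 0 | 4 | 48–52% | 54% |
| 0 | 2.72 | 26–28% | 30% |
| −1 | 6.44 | 67–73% | 75% |
| 0 | 0 | 2.5% | 2.5% |

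The range at 45 per arm comes from the odd participant. With a = 0 and b = 5.44, the expected difference is 5.44 × 22/45 = 2.66 or 5.44 × 23/45 = 2.78. Power is a little below the 80% case because mixing two ranks widens the DISCORD spread: √(4.57² + 5.44²/4) = 5.32.

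**Step 4. What a rank-specific contrast would show.** ACCORD minus second choice:

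- 45 vs 22.5: SE = 4.57 × √(1/45 + 1/22.5) = 1.18; 95% half-width about 2.36.
- 50 vs 25: SE = 4.57 × √(1/50 + 1/25) = 1.12; 95% half-width about 2.23.
- Power by t-test: 62–67% if a = 2.72, and 21–22% if a = 1.36.

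When a = 0 this contrast favours ACCORD significantly in about 2.5% of runs, whatever b is. It carries the information that the pooled test lacks, but imprecisely.

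**Step 5. Do the planned subgroups supply it?** Section 2.8.2 plans an analysis by DISCORD subgroup, and Section 2.1.2 defines those subgroups by exclusion of the recommended formula. A subgroup label that does not follow rank can itself mix second and third choices, and then has the same ambiguity as the pooled arm.

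**The case against.** - **A tie is not an error.** If the pick equals the second choice, the pick is jointly best and the algorithm has not chosen wrongly. This is fair. The claim is plainly false only when a is negative, and the only such row in the table rests on an assumed third-choice gap of 6.44. What stands is that a tie gives no evidence of separating the best formula from both alternatives.
- **No misreport is prescribed.** A reader might infer that the trial will announce the optimal formula whenever the primary test is significant. The article does not say so. The sentence in Section 2.1.1 is design rationale, no decision rule is attached, and the Discussion openly describes the comparison as pooled and admits it cannot show superiority over current practice. It does not, however, address best versus second, and it calls the design appropriate for validating predictive accuracy.
- **The subgroup analysis is already planned.** True, with confidence intervals. The full protocol or analysis plan may define the subgroups by rank. The article neither states nor excludes this, and as written the analysis does not resolve the question.
- **The large percentages need large gaps.** Also true. A gap of 5.44 is 5.44 / 4.57 = 1.19 SD between two active formulas and was chosen so that the pooled difference equals 2.72. At a gap equal to the plan's own 2.72, the figure is 26–30%.

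**Conclusion.** The concern holds as a limit on interpretation. A significant primary result is valid evidence that following the recommendation beats a random choice between the other two formulas. It is not evidence that the recommended formula beats the predicted second choice, which the wording of Section 2.1.1 implies.

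The size is conditional. If the pick only ties the second choice, the primary test favours ACCORD in about 26% to 79% of runs for third-choice gaps of 2.72 to 5.44. If the pick is 1 point worse than the second choice and 6.44 better than the third, it does so in 67–75%. These figures rest on assumed gaps, a common SD of 4.57, and a week-8 t-test in place of the planned mixed model. The ambiguity itself rests on none of them.

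Two stronger readings are not supported. The documents do not show that the third choice is in fact much worse, so the upper percentages are not a forecast. The sample size is also not wrong for the comparison it was set for. Finally, even a clear average advantage over the second choice would not prove optimality for each individual patient.

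**What to change.** Keep the randomisation, sample size and primary test. Then:

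1. Store the three predictions from the locked v1.1 algorithm for every participant at randomisation, before any outcome is seen.
2. Define DISCORD_1 as the formula ranked second by predicted benefit and DISCORD_2 as the one ranked third.
3. Report the week-8 differences ACCORD minus DISCORD_1 and ACCORD minus DISCORD_2 with 95% confidence intervals next to the primary result, as estimates.
4. Word the conclusion from the pooled test as better than the average of the two non-recommended formulas, and discuss optimality only in light of the rank-specific estimates.

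Do not turn the second-choice interval into a pass/fail condition. At 62–67% power for a true advantage of 2.72, and 21–22% for 1.36, such a rule would often withhold a true claim.

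The cost is protocol and analysis wording, since the ranks follow from predictions the algorithm already makes. The downsides are rank-specific intervals with half-widths of about 2.2 to 2.4 points and a more modest headline claim.
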